#### Participant timeline {13}

Work plan and chronogram (Table 1)Phase 1—Preparatory: meeting of all the researchers for the work protocol and the manual of procedures, planning of web-based course, elaborate the course materials and recording of the videos showing the diagnostic and therapeutic manoeuvres on simulated patients

**Table 1 Tab1:** Schedule of enrollment, interventions and assessments

	***Study period***					
	Enrollment	Allocation	Post-allocation			Follow-ups
**Time point**^**a**^	t1		t2	t3	t4	t1–t4
**Enrollment**	x					x
**Eligibility screen**	x					x
**Presentation of the study**			x			x
**Allocation**	x					x
**Interventions**			x			x
**Online training**			x			x
**Face-to-face session**			x			x
**Assessments**				x		x
**Period of information collection**				x	x	x
**Analysis of results**					x	x
**Dissemination of the results**						x

^a^List specific time points: *t1* November 2019 to August 2021, *t2* September 2021 to March 2022, *t3* January 2022 to December 2022, *t4* January 2023 to December 2023

This phase will start in November 2019 and last until March 2021 (this period was extended to May 2021 due to the COVID 19 pandemic). The VERTAP team will meet with the ENT specialist once monthly.

The SIDIAP will randomise the participating centres and assist in defining the study variables.Phase 2: Presentation of the study to 20 PCT in the Southern Metropolitan Area of the Catalan Institute of Health from June to September 2021—participating PCT will be randomly assigned to the IG or the CG.

The IG will start the course at the beginning of the study, and PCT in the CG will start the training after the study follow-up period has ended.

The PCT in the IG will access the course online platform during November and December 2021. The face-to-face sessions will take place from January to April 2022.Phase 3: The period of information collection will be extended to January 2022 to December 2022.Phase 4: Analysis of results—data will be analysed by the researchers and a statistician. Manuscript writing will last from January to March 2023. The results will be published in scientific journals and disseminated in national and international conferences.

#### Sample size {14}

To improve vertigo diagnostic codes, accepting an alpha risk of 0.05 and a beta risk < 0.2 in a two-sided test, a total of 356 patients are needed per group (IG and CG) to detect as statistically significant a difference of 30% and 40% in correct diagnoses (BPPV, vestibular neuritis, vestibular migraine and Menière’s disease) for the CG and IG, respectively, with no loss to follow-up anticipated (GRANMO calculator, Institut Municipal d’Investigació Mèdica, Barcelona, Spain, using the ARCSINUS approach). To evaluate the final sample size, we take into account that the intercluster correlation coefficient (ICC) most commonly used in cluster-randomised trials in PC is 0.05. This ICC translated to a size of 45 individuals (assuming 10 clusters per group) in the design is adjusted by 1.24, i.e. *n* = 712 × 1.24 = 884 (45 per centre).

Similarly, the comparison of expected variation proportions for the prescription of antivertigo agents is 58.21% and 48% for the CG and IG, respectively (374 per group before adjustment by design) and 20% and 10% for referrals to neurology and ENT (195 per group before adjustment for design). All proportion estimates are based on the results of the previously published study [20].

However, data from *all* patients with a new diagnosis of vertigo and dizziness during the study period (1 year after the intervention) in participating centres will be collected, ensuring a number greater than the sample calculation.

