#### Data management {19}

Clinical trial data will be entered electronically. Variables will be extracted from the SIDIAP before starting the training and quarterly during the 12 months after the start of the trial. The data of all patients with a new diagnosis of vertigo and dizziness in participating centres will also be collected, ensuring a sample size greater than necessary. The files will be safely stored in numerical order in one location for a period of 3 years after the end of the study. Only SIDIAP staff will be able to export these data.

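### The design effect of 1.24 contradicts the stated ICC of 0.05 with 45 patients per team (which give 3.2); at that ICC, power is about 40%, not 80%, and more patients in 20 teams cannot restore it

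*Protocol article*

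**What the plan says.** Sample size {14} sets the error rates by "accepting an alpha risk of 0.05 and a beta risk < 0.2 in a two-sided test" and the target as "a difference of 30% and 40% in correct diagnoses" for control and intervention. Before clustering, "a total of 356 patients are needed per group (IG and CG"), by the arcsine method. For clustering it says that the "ICC) most commonly used in cluster-randomised trials in PC is 0.05", and continues: "This ICC translated to a size of 45 individuals (assuming 10 clusters per group) in the design is adjusted by 1.24". It multiplies 712 by 1.24 to reach 884, given as 45 per centre. Study setting {9} and Recruitment {15} both fix 10 PCT per arm.

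The same section adds that data on every patient with a new diagnosis of vertigo or dizziness in the participating centres will be collected, "ensuring a number greater than the sample calculation". Data management {19} repeats this as "ensuring a sample size greater than necessary".

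**The concern.** The ICC, the cluster size and the inflation factor appear together, and the first two do not give the third. The usual variance inflation for equal clusters is 1 + (m − 1) × ICC. At m = 45 and ICC 0.05 it more than triples the sample, whereas the protocol adds 24%.

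The 80% power for the primary outcome rests on this factor. If the ICC is right, a true 10-point gain in specific diagnoses would more likely be missed than found, and a null result could be read as evidence of no effect from an adequately powered trial. The promise to collect all patients makes this harder to see. It counts patients, but once clusters are large the limiting quantity is the number of PCT.

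**Working it through.** **Inputs, all from Sample size {14}:** two-sided α = 0.05; power 80%; p = 0.30 and 0.40; ICC ρ = 0.05; m = 45 patients per PCT; k = 10 PCT per arm.

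**1. Reproduce the unadjusted size.** The arcsine effect is h = 2·arcsin√0.40 − 2·arcsin√0.30 = 0.2102. Then n = 2(1.960 + 0.842)²/h² = 2 × 7.849/0.04417 = 355.4, so 356 per arm and 712 in total. This agrees with the protocol. The multiplication also agrees to within rounding: 712 × 1.24 = 882.9, and 884/20 = 44.2, rounded up to 45 per centre.

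**2. Design effect.** DE = 1 + (45 − 1) × 0.05 = **3.20**. The factor 1.24 does not follow:

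- at m = 45 it needs ρ = 0.24/44 = 0.0055, about one ninth of the stated value;
- at ρ = 0.05 it needs m = 1 + 0.24/0.05 = 5.8 patients per PCT.

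Other readings also fail: m = 44.2 gives 3.16; m = 35.6 (356/10) gives 2.73; using the number of clusters in place of m gives 1.45 (10) or 1.95 (20); √3.2 = 1.79.

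**3. Power at ρ = 0.05.** Effective size per arm is n_eff = km/[1 + (m − 1)ρ]. Power is Φ(h√(n_eff/2) − 1.96). The t version uses a noncentral t on 2k − 2 = 18 df with noncentrality 0.10/√(0.45/n_eff), where 0.45 = 0.3 × 0.7 + 0.4 × 0.6.

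| Patients per PCT | n_eff per arm | Power, normal | Power, t on 18 df |
|---|---|---|---|
| 45 | 450/3.2 = 140.6 | 42% | 39% |
| 100 | 168.1 | 49% | 45% |
| 200 | 182.6 | 52% | 48% |
| 500 | 192.7 | 54% | 50% |
| no limit | k/ρ = 200 | 56% | 51% |

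**4. Can more patients rescue it?** The target is n_eff ≥ 356, but with 10 PCT per arm n_eff stays below 10/0.05 = 200. Even with unlimited patients, more than 356 × 0.05 = 17.8 PCT per arm would be needed, so at least 18.

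**5. What a factor of 3.2 implies.** The total is 712 × 3.2 = 2,278, but only at 45 per PCT: 1,139/45 = 25.3, so 26 PCT per arm. Placing 2,278 patients in 20 PCT (about 114 each) raises the design effect to 1 + 112.9 × 0.05 = 6.65 and gives n_eff = 1,139/6.65 = 171 per arm and power of about 49%.

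**6. Detectable difference at 80% power, control 30%.** At 45 per PCT, intervention about 46% (47% with t). With unlimited patients, about 43% (44% with t).

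**7. The other branch.** If ρ were 0.0055, then DE = 1.24, n_eff = 450/1.24 = 363 per arm, and power at 45 per PCT is 81% (77% with t). The largest ICC compatible with n_eff = 356 in 10 PCT per arm is (450/356 − 1)/44 = 0.006 at m = 45, and 10/356 = 0.028 with unlimited patients.

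**The case against.** The arithmetic slip cannot be defended, but its consequences can be argued about.

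- **Which number is wrong is unknown.** If the ICC was meant to be near 0.005, the factor is roughly right and so is the power. This stands as a possibility, but the text says 0.05 and defends it as the usual value in primary care trials. The power figures here are therefore conditional on the stated ICC.
- **The trial will not stop at 45 per PCT.** True. At ICC 0.05 the relevant normal-approximation range is 42% to 56%. Numbers of vertigo patients per PCT are not given, so it cannot be narrowed. No value in it approaches 80%.
- **A pre-intervention year is available.** Using each PCT's 2021 proportion as a covariate would raise the ceiling to about 200/(1 − r²) per arm, where r is the between-year correlation of PCT proportions. This passes 356 once r exceeds √(1 − 200/356) = 0.66. The point is fair, and the ceiling in this review is accordingly one for an unadjusted comparison. But the sample size section claims no such gain, Statistical methods {20a} names a t-test and no such covariate, and r is not given anywhere.
- **The ceiling does not apply equally to every outcome.** Correct. For referrals (20% versus 10%) the same limit is about 80–81% by the normal approximation. For antivertigo agents (58.21% versus 48%) it is about 53–54%. The statement that 80% is out of reach concerns the primary outcome, and the antivertigo outcome likewise.

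**Conclusion.** The concern holds. The stated ICC and cluster size give a design effect of 3.2, and no reading of the stated inputs produces 1.24. At ICC 0.05, unadjusted power for 30% versus 40% is about 40% at 45 patients per PCT (42% normal, 39% t) and at most 51–56% however many patients are collected in 20 PCT. The claim that collecting all patients secures the required size is true of the headcount only, not of the power the headcount was meant to deliver.

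These figures assume equal cluster sizes, which is favourable because unequal sizes lower power, and no baseline adjustment, which is what the document describes. If an ICC near 0.0055 was intended, the stated power is about right, but the document says otherwise. As written, a reader cannot tell a trial with about 40% power from one with about 80%.

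**What to change.** In Sample size {14}, decide whether the ICC or the factor is the slip, and make the paragraph consistent.

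- **If ICC 0.05 stands:** give the design effect as 3.2 at 45 per PCT. Report unadjusted power of about 40% at that size and at most 51–56% with all patients collected. Give the detectable difference with its condition: 30% versus about 46–47% at 45 per PCT, or about 43–44% as the limit for very large clusters.
- **If 1.24 was meant:** state the implied ICC of about 0.0055 and justify it, since it replaces a value the text calls the usual one.
- **In either case:** delete the reassurance about exceeding the required size here and in Data management {19}, or replace it with the effective sample size expected from the PCT actually enrolled. Power may be recalculated with adjustment for each PCT's pre-intervention proportion, provided that the assumed correlation is stated and the analysis section names that adjustment.

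The cost is rewording and, if 0.05 stands, a less favourable power statement. Conduct does not change and no PCT need be added for this correction, so it can still be made although Trial status reports the training as delivered.

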#### Plans to promote participant retention and complete follow-up {18b}

After randomisation, the IG will make every reasonable effort to complete the study. The anticipated annual loss-to-follow-up is ≤ 5%. Physicians in the IG should commit to take the online and face-to-face course and apply the procedures learned during the study.

The PCT of Catalonia are currently focused on the COVID-19 pandemic. However, it is expected that PCT will resume normal primary care activities shortly. To increase adherence to the online course, participants will receive a weekly email reminder. To optimise participation in the face-to-face session in each PCT, we will contact the PCT director so that they decide the best date within a 4-month period. A pair of researchers will go to each PCT to deliver the face-to-face session.

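### The sample-size paragraph and the retention section disagree on loss, the antivertigo size is left unadjusted for clustering, and the factor 1.24 does not follow from an ICC of 0.05 with 45 patients per team

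*Protocol article*

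**What the plan says.** All references are to the protocol article.

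Sample size {14} sets the error rates by "accepting an alpha risk of 0.05 and a beta risk < 0.2 in a two-sided test". For the primary outcome it takes "a difference of 30% and 40% in correct diagnoses" and arrives at 356 per group by the arcsine method, "with no loss to follow-up anticipated". It then quotes an ICC of 0.05, 45 individuals per centre and 10 clusters per group, uses a design factor of 1.24, and reports 712 × 1.24 = 884.

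The next paragraph handles two secondary outcomes. For antivertigo prescribing the rates are "58.21% and 48% for the CG and IG" and the size is "374 per group before adjustment by design". For referrals (20% and 10%) it is 195 per group, also before adjustment. Neither is carried through to an adjusted total. The section closes by saying that all newly diagnosed patients in the participating centres will be collected, so that the number will exceed the calculated one.

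Plans to promote participant retention and complete follow-up {18b} states: "The anticipated annual loss-to-follow-up is ≤ 5" per cent. It does not say whose loss this is.

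**The concern.** Three statements in or around one calculation do not fit together.

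- Loss is zero in one section and up to 5% in another. The primary size has almost no margin, so a 5% patient loss takes it below the target.
- The antivertigo outcome needs more patients than the primary outcome before adjustment (374 against 356), and its adjustment is left unfinished.
- The design factor that turns 712 into 884 is much smaller than the stated ICC and cluster size imply.

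The first two concern a couple of percentage points of power. The third decides whether the trial has anything near 80% power for its primary outcome, and whether collecting every eligible patient can make up a shortfall.

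**Working it through.** **Inputs (Sample size {14} unless noted).** Two-sided alpha 0.05; power 80%; rates 30% v 40% (primary), 58.21% v 48% (antivertigo), 20% v 10% (referrals); ICC 0.05; 45 per centre; 10 centres per group; factor 1.24; loss 0% here and up to 5% in {18b}.

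**1. The unadjusted sizes reproduce.** With h = 2·asin√p1 − 2·asin√p2 (absolute value) and n per group = 2·((1.960 + 0.842)/h)²:

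| Outcome | h | n computed | n stated |
|---|---|---|---|
| Primary | 0.210 | 355.4 | 356 |
| Antivertigo | 0.205 | 373.7 | 374 |
| Referrals | 0.284 | 194.9 | 195 |

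**2. The total of 884 reproduces if 1.24 is taken as given.** 356 × 1.24 = 441.4, rounded up to 442 per group, which is 884.

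**3. Power at 884 with factor 1.24.** The effective size is 442/1.24 = 356.5 per group. Power = Φ(h·√(n_eff/2) − 1.960).

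- Primary: 80.1%.
- Antivertigo: 78.1%.
- Referrals: 96.6%.

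The adjusted antivertigo size would be 2 × 374 × 1.24 = 927.5, so 928, which is 44 more than 884. At 45 × 20 = 900 patients, antivertigo power is 78.8%.

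**4. Effect of a 5% loss, if it is patient loss.** 884 × 0.95 ≈ 840, an effective size of about 339 per group.

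- Primary power: 78.1%.
- Antivertigo power: 76.0%.
- Total that restores the primary size: 884/0.95 = 930.5, so 931.

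**5. The design factor.** The usual formula is 1 + (m − 1) × ICC. With m = 45 and ICC 0.05 it gives 1 + 44 × 0.05 = 3.2. Using the unadjusted 35.6 per centre (356/10), it is still 1 + 34.6 × 0.05 = 2.73. A factor of 1.24 at m = 45 requires an ICC of 0.24/44 = 0.0055, about one ninth of the stated value.

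**6. Power at 884 with factor 3.2.** The effective size is 442/3.2 = 138.1 per group.

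- Primary: 41.5% by the arcsine formula, 41.3% by the pooled normal formula.
- Antivertigo: 39.9% and 39.7%.
- Raising the total to 928 gives antivertigo only about 41%.

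The totals needed at 45 per centre are 712 × 3.2 = 2,278.4 (2,279) and 748 × 3.2 = 2,393.6 (2,394). Divided by 45, these are about 51 and 53 teams, not 20.

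**7. Ceiling with 10 teams per arm.** The effective size per group is 10m/(1 + (m − 1) × 0.05). As m grows this approaches 10/0.05 = 200, below both 356 and 374. At 200 per group:

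- Primary: Φ(0.2102 × 10 − 1.960) = Φ(0.142) ≈ 56%.
- Antivertigo: Φ(0.2050 × 10 − 1.960) = Φ(0.090) ≈ 54%.

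**The case against.** The strongest reply has four parts.

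- **884 belongs to the primary outcome.** A reader might infer that 884 fails the plan's own requirements because antivertigo prescribing needs 928. The text does not support that. Outcomes {12} lists antivertigo prescribing as secondary, its size is openly labelled as unadjusted, and nowhere is 80% power at 884 claimed for it. A trial need not be sized on its most demanding secondary outcome. This stands, and it makes the 928 a minor point.
- **884 is a minimum.** All eligible patients are extracted, so 44 more patients, or a 5% loss, would matter little. This stands only if 1.24 is right. At an ICC of 0.05 extra patients in the same 20 teams cannot bring power to 80%.
- **The 5% may concern physicians.** The neighbouring sentences in {18b} are about intervention-group physicians finishing the course, and outcomes come from a database extraction. Patients who die or change team (Eligibility criteria {10}) are exclusions and need not be losses from the analysed number. So a flat statement that primary power is below 80% because of loss goes further than the document allows. The two sections still need one stated meaning.
- **The shortfalls of about 2 to 4 points are small.** True under 1.24, but those figures rest on a factor that contradicts the stated ICC.

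**Conclusion.** The point holds in this form.

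- **Loss.** The two sections disagree. The cost is about 2 points of primary power (80.1% to 78.1%), conditional on the 5% being patient loss and on factor 1.24.
- **Antivertigo.** The adjustment is unfinished. With 1.24, 884 gives 78.1% power. This is minor.
- **Design factor.** 1.24 does not follow from ICC 0.05 and 45 per team, and this is the material error. With 3.2, 884 gives about 41% (primary) and 40% (antivertigo), with ceilings of about 56% and 54% at 10 teams per arm.

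The power figures take the plan's rates as given and assume equal cluster sizes. The document does not show which of 0.05 and 1.24 was intended. If the ICC is really about 0.0055, the primary size is close to right and a modest surplus of patients covers the other two points. If it is 0.05, a reader should not infer that complete extraction rescues the power.

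**What to change.** 1. Use one loss assumption in Sample size {14} and in the retention section {18b}, and say whether it concerns patients or physicians. If patients, carry it into the total.
2. Make the ICC and the design factor agree: either apply 1 + 44 × 0.05 = 3.2, or state and justify the ICC of about 0.0055 that 1.24 implies.
3. Restate the power actually held with 10 teams per arm for the primary outcome, antivertigo prescribing and referrals. It is enough to state antivertigo power; the trial need not be resized on it.
4. If the ICC stays at 0.05, remove any suggestion that extracting more patients per team restores 80% power.

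The text change is about one paragraph plus one sentence in {18b}. The cost in content depends on item 2. Under an ICC of 0.0055 the stated power barely moves. Under 0.05 the plan must acknowledge primary power of at most about 56%, and only more teams, not more patients per team, could reach 80% for the differences assumed.

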#### Recruitment {15}

Recruitment will be carried out in the Primary Care Management of the Southern Metropolitan Area of the Catalan Institute of Health, which in 2016 had 53 PCT for a catchment population of 1,334,381 people, of whom 1,042,920 had been visited during that same year. A random sample of 20 PCT will be chosen from the 53; 10 will be included in the IG and 10 in the CG.

Each primary health centre will be personally visited to offer physicians the possibility of participating in the study.

### Assignment of interventions: allocation

We have included all the “Metropolitana Sud” PCT.We have excluded centres that have taken BPPV courses and training.We have excluded the paediatric centres and PCT in prisons.From the remaining centres, a random function has selected 30 centres. A second randomisation has classified these PCT into two groups (control and intervention).

#### Sequence generation {16a}

From a list of 56 potential PCT, we will exclude the centres that have received training in vertigo in the last 5 years. Next, we will conduct two random processes using the RAND function in MySQL as follows: (1) a random selection of 30 of the remaining PCT (2) will be assigned to treatment groups (sampling without replacement a vector of 15 controls and 15 interventions).

#### Concealment mechanism {16b}

Randomisation will be applied to a list of PCT in the Southern Metropolitan Area of the Catalan Institute of Health. In consecutive order, we will inform the management teams of the centres and ask for their participation. We will hold informative sessions in the centres that accept participation and exclude the centres where intended participation is under 60% of professionals. The first eligible 10 PCT from each treatment group will define the final sample.

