#### Implementation {16c}

The selection and assignment randomisations will be carried out by an external SIDIAP data manager. The researchers will contact the PCT managers to inform them. If managers agree to participate, a pair of researchers will attend the PCT and if 60% of the PCT professionals agree, they will be randomly assigned to the IG or the CG prior to the presentation session.

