## Statistical methods

### Statistical methods for primary and secondary outcomes {20a}

Data analyses will follow Consort Cluster recommendations (http://www.equator-network.org/reporting-guidelines/consort-cluster/), and intention-to-treat analysis will be used for comparisons between the groups. We will firstly analyse the baseline comparability of the two groups to verify homogeneity regarding study variables. Descriptive statistics will be performed for all baseline variables, using Student’s *t* or Mann-Whitney *U* test for quantitative variables, and chi-square or Fisher’s exact test for categorical variables.

The *t*-test will evaluate differences in outcome variables between the groups pre- and post-intervention. Logistic regression multivariate analysis will be performed to analyse the relationship between baseline variables of primary care centres and professionals, and outcome variables. Significance will be set at 5% for all analyses. Statistical software R (revised version 3.2.4) will be used.

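### The protocol gives two opposite orders for allocation and agreement; if arms were fixed first, teams are dropped on willingness after randomisation and the analysed set is not intention-to-treat

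*Protocol article*

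**What the plan says.** Four places put allocation first.

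- Assignment of interventions: allocation, in the past tense: "From the remaining centres, a random function has selected 30 centres", followed by a second randomisation into the two groups.
- Sequence generation {16a} fixes the split: "sampling without replacement a vector of 15 controls and 15 interventions".
- Concealment mechanism {16b} then recruits: "In consecutive order, we will inform the management teams of the centres and ask for their participation". The researchers will "exclude the centres where intended participation is under 60% of professionals", and "The first eligible 10 PCT from each treatment group will define the final sample".
- Table 1 places allocation at t1 and the presentation of the study at t2.

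Two places put agreement first. Implementation {16c} says that "if 60% of the PCT professionals agree, they will be randomly assigned to the IG or the CG prior to the presentation session". The Phase 2 text under Participant timeline {13} assigns PCT that are already participating.

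On analysis, section {20a} states that "intention-to-treat analysis will be used for comparisons between the groups", and section {20c} repeats it. Eligibility criteria {10} exclude PCT that are not interested. They also exclude patients who die in the year before or after the training, and patients who change PCT.

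**The concern.** In a cluster trial the randomised comparison is protected if clusters agree before anyone involved knows their arm, or if every cluster approached is analysed in its arm whether or not it agreed. The order set out in {16a} and {16b} secures neither.

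Willingness may also mean different things by arm. An intervention-group (IG) team agrees to a course of about 14 hours plus a 90-minute session now. A control-group (CG) team agrees to take part and is offered the same training after the study. If willingness goes with how a team codes vertigo, and does so differently in the two arms, the groups can differ before any training takes place. The primary outcome is how physicians code, so such a link is plausible. The document neither shows it nor rules it out.

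**Working it through.** **1. The two orders side by side**

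| Step | Allocation section, {16a}, {16b}, Table 1 | {16c}, Phase 2 text |
|---|---|---|
| First | 30 PCT drawn and split 15:15 | Manager and 60% of professionals agree |
| Second | Managers approached, 60% rule applied | PCT assigned to IG or CG |
| Third | First 10 eligible kept in each arm | Presentation session |

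Both cannot describe what was done. The second order is also not wholly clear. Section {16c} assigns before the presentation session, while section {26a} takes physicians' consent after an explanatory session. If these are the same session, physicians consent after assignment even on the favourable order.

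**2. Count.** Under the first order 15 + 15 = 30 PCT are randomised and 10 + 10 = 20 are kept. Up to 10 of 30 (33%), or 5 of 15 per arm, are not analysed. Some of these may never have been approached because 10 had already been found. Under the second order all assigned PCT could be analysed.

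**3. The plan's own figure.** Sample size {14} gives 30% against 40%, two-sided alpha 0.05, power 80%, 356 per group. Arcsine formula: n = (1.960 + 0.842)² / [2(asin√0.30 − asin√0.40)²] = 355.4, so 356 reproduces.

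**4. Spread between PCT.** With 30% specific diagnoses and the stated ICC of 0.05, SD = √(0.05 × 0.30 × 0.70) = 0.102, or 10.2 points.

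**5. Shift if only the IG is selected.** Assume that the refusing IG teams are exactly the least motivated of those approached, and that motivation has correlation r with the PCT's proportion. Then shift = k × r × 10.2 points, where k is the expected mean of the 10 highest of the normal scores of the PCT approached.

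| IG teams approached | k | r = 0.2 | r = 0.3 | r = 0.5 |
|---|---|---|---|---|
| 12 (2 refuse) | 0.28 | 0.6 | 0.9 | 1.4 |
| 15 (5 refuse) | 0.52 | 1.1 | 1.6 | 2.6 |

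The values of r and the numbers approached are assumptions.

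**6. Simulation of the first-10-willing rule, no true effect.** Assumptions: 15 PCT per arm in random contact order, acceptance about 75%, 45 patients per PCT, cluster-level t-test, 4,000 trials per scenario. An arm with fewer than 10 acceptors keeps those it has.

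| Link between acceptance and the PCT's proportion | Bias (points) | Type I error |
|---|---|---|
| None | 0.0 | 0.053 |
| Equal in both arms | 0.0 | 0.054 |
| IG only, log-odds 0.5 per SD | +1.3 | 0.056 |
| IG only, log-odds 1 per SD | +2.5 | 0.064 |
| Opposite directions by arm, log-odds 1 per SD | +4.9 | 0.145 |

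With 40,000 trials the two IG-only rows gave type I error 0.055 and 0.071, with the same bias to within 0.1 point. Reversing the sign of the IG link reverses the sign of the bias.

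**The case against.** The strongest reply is that {16c} describes a sound order. If it is what was done, the cluster-level objection falls away and only the wording needs correcting. That stands, and it is why the conclusion is conditional.

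Several stronger readings are tempting but not supported.

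- **The arm was open to the recruiters.** The text does not say so. An external SIDIAP data manager runs both randomisations, and the open-label statement in {17a} concerns blinding. Concealment is undocumented, not shown to be absent.
- **Only the IG was filtered for motivation.** The interest criterion, manager agreement and 60% rule apply to both arms, and CG teams are promised the training later. Only a difference in degree can be argued.
- **The bias favours the intervention.** Teams that code poorly might want training most, which would reverse the sign.
- **A third of PCT are discarded in a harmful way.** The rule keeps the first 10 eligible, not the 10 keenest of 15. PCT never approached do no harm if the contact order is random. The 15-approached row above is therefore an upper case.
- **A sample of 20 contradicts a draw of 30.** Study setting {9} and Recruitment {15} can be read as loose summaries of drawing 30 to obtain 20.

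The 2021 baseline year would also reveal a starting difference in coding, and {20a} checks baseline comparability. That helps with detection. It does not restore the randomised comparison, and the article does not commit to adjusting for baseline.

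**Conclusion.** The contradiction in order is certain. If the order in {16a}, {16b} and Table 1 was followed, clusters were excluded on willingness after allocation, and the set analysed is not intention-to-treat as {20a} and {20c} declare.

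Recruitment bias is then a risk, not an established fact, and its direction is unknown. Its size is about zero if acceptance is unrelated to the PCT's proportion or equally related in both arms. It is roughly 1 to 3 points of the planned 10 under illustrative selection in the IG only, and larger only if selection runs in opposite directions by arm. These sizes rest on the stated ICC of 0.05 and on assumed links between willingness and coding. They shrink with the square root of the ICC and with the number of teams that refuse.

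A smaller, separate departure is at patient level: excluding patients for death after the training, or for a change of PCT if that occurs after it, also removes people on the basis of events after allocation.

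**What to change.** 1. State one sequence, and make Study setting {9}, Participant timeline {13} with Table 1, Recruitment {15}, the allocation section, and {16a} to {16c} agree with it. The manager's agreement and the 60% check are settled first. Only then does the SIDIAP data manager reveal the arm to the researchers and the PCT.
2. Trial status reports recruitment since October 2021 and the course completed in December 2021, so this may come too late to change conduct. If arms were known at approach, say so, and report PCT approached, refusing and excluded under the 60% rule, by arm.
3. In that case analyse all approached PCT in their randomised arm from SIDIAP, if extraction is permitted for PCT that declined. Show the 20 participating PCT as a second set, and adjust for each PCT's 2021 proportion. Do not use all 15 against 15 as the main set, because it would count as trained some IG teams that were never offered training.
4. Separately, keep patients who die or change PCT after the intervention starts, and count their events in the original PCT's arm up to exit.

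The cost is wording, a somewhat larger extraction and some dilution. If 12 IG teams were approached and 2 refused, a 10-point effect becomes 10 × 10/12 = 8.3 points, and the arcsine requirement before clustering rises from 356 to 507 per group. With 5 refusals among 15 it becomes 6.7 points and about 783. Because all eligible patients in the PCT are to be extracted, patient numbers are unlikely to be the constraint; the number of PCT is.
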